## Abstract

**Background:**

Chronic lymphocytic leukemia (CLL) is a type of cancer that affects the blood and bone marrow, and it is the most prevalent form of leukemia in adults. Many patients experience symptoms that can significantly impact their quality of life, particularly in terms of physical ability, emotional health, and fatigue. Therapeutic exercise has shown to be an effective intervention for alleviating both physical and psychological symptoms in these patients. Specifically, strength training may help address some common treatment side effects.

**Objective:**

This study aims to evaluate the effects of a therapeutic exercise program, focused on frailty in patients with CLL, along with secondary objectives including impacts on functional capacity, quality of life, psychological status, sleep quality, body composition, anthropometric variables, lipid profile and on proteins related to the immune system and inflammation.

**Methods:**

An open label, randomized controlled trial will be carried out with 36 participants, divided into an intervention group (supervised resistance training twice a week and home exercises) and a control group (home exercise only). The primary outcome measure is fraility, assessed using Short Physical Performance Battery (SPPB). Secondary outcomes include assessments using HADS, FACT-F, EORTC QLQ-C30, EORT QLQ-CLL17.

**Results and conclusions:**

This study will explore how physical exercise can improve quality of life and various health metrics in patients with CLL. By creating customized exercise protocols, the research seeks to boost patient well-being, improve treatment outcomes, and lessen debilitating side effects, ultimately promoting the integration of physical activity into routine care.

**Clinical Trial Registration:**

ClinicalTrials.gov, identifier (NCT06654206).

## Introduction

1

Chronic lymphocytic leukemia (CLL) is a malignant hematological disease that mainly affects older people, with a mean age at diagnosis of about 70 years, and is the most common form of leukemia in adults (1, 2). It has an incidence of 4–5 cases per 100,000 people in Western countries, accounting for nearly 30% of all adult leukemias (3). This condition is characterized by an accumulation of mature B lymphocytes in the blood, bone marrow, and lymph nodes. Its progression is generally slow, though the clinical development can vary: some patients remain stable for years without needing treatment, while others require early medical intervention (4).

As CLL progresses, many patients experience symptoms that affect their quality of life, especially regarding functional capacity and emotional well-being. Fatigue is one of these most characteristic symptoms (5), and directly correlates with muscle weakness, lack of energy, and a consequent loss of physical functionality, leading to limitations in daily activities, reduced mobility, and, ultimately, a loss of autonomy and social interaction (6). Additionally, side effects from CLL treatments, such as BTK inhibitors, BCL2 inhibitors and monoclonal antibodies can exacerbate this functional decline, creating a cycle of physical and emotional limitations that severely impact quality of life.

The frailty phenotype involving five domains [unintentional weight loss (10 lbs in past year), self-reported exhaustion, weakness (grip strength), slow walking speed, and low physical activity], and characterizes physical frailty as a subset of frailty (7). In turn, sarcopenia was redefined in 2019 by EWGSOP2 (8) and is now considered a syndrome characterized by progressive and generalized decline in muscle mass, strength and function, associated with age and leading to adverse events. Considering this, physical frailty and sarcopenia are strongly related and sarcopenia has been described as the biological substrate of physical frailty (9).

The emotional aspect also plays a crucial role in CLL patients. Literature suggests that the diagnosis and course of this chronic disease generate high levels of stress, anxiety, and depression—emotions that affect perceived control over the disease and the adaptation to the diagnosis (10). This emotional burden not only worsens other physical symptoms but can increase fatigue and reduce motivation to participate in physical and social activities.

In light of these clinical challenges, therapeutic exercise has proven to be a promising intervention for improving both physical and psychological symptoms in these patients (11–15). Specifically, strength training could help manage some of the common adverse effects of CLL. Strengthening muscles and increasing muscle mass helps counteract weakness and improve functional capacity, promoting independence in daily activities and reducing feelings of fatigue (16). Additionally, strength training could improve bone health, joint stability, and balance, which are often compromised in CLL patients, increasing the risk of falls and fractures (17).

Furthermore, recent pilot studies have shown that different types of exercise can be beneficial for patients with chronic lymphocytic leukaemia. Moderate-intensity aerobic activity can improve cardiorespiratory fitness, reduce chronic fatigue and strengthen the immune system (18) and high-intensity interval training (HIIT) with strength training had strong effects on muscle strength and immune function in previously untreated older adults with CLL (19), all of which are crucial for patients with haematological diseases such as CLL. In this regard, a training intensity of 70% of the 1-RM with 12 repetitions has been selected, as previous studies have indicated that lower intensities may not provide a sufficient stimulus to counteract sarcopenia and the functional decline associated with the disease and its treatments (20). Therefore, this approach has been considered optimal for maximizing benefits without compromising patient safety.

It is also hypothesized that strength training could be particularly beneficial given the clinical characteristics of the disease. CLL is characterized by immune dysfunction and a high risk of sarcopenia and bone density loss, which can significantly reduce patients’ physical functionality. Muscle strengthening through resistance training could mitigate these effects, contributing to improved muscle and bone health. Furthermore, strength training could reduce the risk of falls and fractures, which are common issues in this population.

On the other hand, physical activity appears to have positive emotional effects, including reductions in anxiety and depression, which promotes better sleep (21). Beyond its physiological benefits, regular exercise contributes to improved self-esteem and self-perception, offering patients a sense of control over their health. This is especially relevant in chronic diseases like CLL, where patients often feel a loss of control (22). Thus, exercise could not only improve quality of life but also provide a tool for facing emotional challenges related to disease, particularly relevant consideration in a long-term illness.

Despite this evidence, there is still limited research on the benefits of strength training in cancer patients, and specific studies on the effects of strength training programs in CLL are particularly lacking. Most studies have focused on more prevalent cancers, such as breast or prostate cancer, leaving a gap in knowledge about the impact of exercise on hematological diseases like CLL. Specifically, studies exploring how strength training influences specific aspects of health in these patients are needed.

In this context, our study aims to contribute to the existing knowledge by evaluating the effects of a therapeutic exercise program focused on strength training on general functional capacity and quality of life in CLL patients. That is why we propose a study protocol that addresses all these clinical challenges in this type of patients, aiming to help establish evidence-based clinical intervention protocols in the future.

As the primary objective, we aim to evaluate the effects of a supervised therapeutic exercise program, focused on strength training, on frailty in patients undergoing treatment for CLL. And as secondary objectives, the following:
•To characterize and describe the functional and psychological status of participants treated for CLL.•To assess the impact of a therapeutic strength-based exercise program on quality of life in participants under treatment for CLL.•To assess the impact of a therapeutic strength-based exercise program on sleep quality in participants under treatment for CLL.•To evaluate the impact of a therapeutic strength-based exercise program on specific aspects of functional physical capacity in participants treated for CLL, including fatigue, upper and lower limb strength and walking speed.•To assess the impact of a therapeutic strength-based exercise program on psychological well-being in participants with treatment for CLL, with a focus on anxiety and depression.•To evaluate the impact of a therapeutic strength-based exercise program on body composition and other anthropometric variables in participants under treatment for CLL.•To assess the impact of a therapeutic strength-based exercise program on lipid profile and on proteins related to the immune system and inflammation.

## Methods and analysis

2

### Study design and setting

2.1

An open-label, randomized controlled trial will be carried out at the University of Salamanca's Faculty of Nursing and Physiotherapy (Spain), adhering to the Consolidated Standards of Reporting Trials (CONSORT) guidelines (23). The current treatment protocol is detailed based on SPIRIT recommendations (24). A detailed overview of participant enrolment, interventions, and assessments is provided in the Supplementary Material (Supplementary Table S1). The Research Ethics Committee for Medicinal Products of the IBSAL-Hospital Universitario de Salamanca has approved the trial protocol (record number2024/11), and the study will be conducted in compliance with the Declaration of Helsinki. This clinical trial has been registered on ClinicalTrials.gov (NCT06654206).

### Participants and eligibility criteria

2.2

Participants diagnosed with Chronic Lymphocytic Leukemia (CLL) undergoing active treatment will be recruited from the Hematology Department of the Hospital Universitario de Salamanca.

The inclusion criteria are as follows:
•Participants diagnosed with CLL or Small Lymphocytic Lymphoma (SLL) undergoing active treatment.•Participants who have not engaged in regular physical activity in the past 8 weeks.•Performance Status (ECOG) 0–1.•Signed informed consent.The exclusion criteria are:
•The presence of any medical contraindications to physical exercise, such as severe musculoskeletal disorders, serious cardiovascular diseases, bone metastases, or other conditions as determined by a healthcare professional.•Participants unable to complete the initial evaluation tests or who have difficulty performing basic exercises.•Other circumstances, as determined by the researchers, that may interfere with the study's objectives or development.Participants will be discontinued if they meet any of the following:
•Negative developments or progression of the tumor process.•Severe adverse events related to exercise.•Voluntary withdrawal from the intervention.•New medical contraindications that prevent safe participation.•Non-adherence to the intervention protocol that compromises study integrity.These criteria ensure participant safety and adherence to ethical research guidelines.

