### Outcomes

2.4

During the initial assessment, all variables, including sociodemographic factors, will be measured. After the intervention period, all outcome variables will then be evaluated again.

Personal and sociodemographic variables are as follows:
•Age (years)•Gender (male/female)•Weight (kilograms), height (meters) and body mass index (kg/m^2^)•Time since diagnosis (years and months)•Diagnosis (CLL or small lymphocytic lymphoma)•IGHV mutational status (mutated/unmutated)•Number of prior lines of treatment•Current treatment and dose•Time under current treatment (months)•Chromosome 17p deletion and *TP53* mutation status prior to current treatment (present/absent)•Current treatment under clinical trial (yes/no)

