
### Sample size

2.5

The sample size was determined based on functional capacity, assessed by the Short Physical Performance Battery (SPPB) with scores ranging from 0 to 12 points (27). According to previous research in subjects with similar characteristics, 1.34 points has been established as a substantial minimum demonstrable change, in order to avoid detection of small and irrelevant changes (44). Furthermore, in studies with interventions shorter than 12 weeks, with similar participants, the standard deviation of the SPPB has been estimated to range between 1 and 1.5 points (45, 46).

Considering these data, the sample size calculation to detect a difference equal to or greater than 1.34 points on the SPPB, with a standard deviation of 1.3 points, accepting an alpha risk of 0.05 and with a power of 80%, requires 18 participants in each group, also assuming a loss rate of 15%. This calculation was performed with GRANMO software version 7.12.

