### Limitations

3.2

This study presents three main limitations. First, the progression of the disease itself, as well as tumor-related complications, may result in participant dropout. Second, the presence of comorbidities, whether pre-existing before the cancer diagnosis or arising as a consequence of the disease and its treatment, could affect the standardization of interventions. However, these limitations are inherent to any complex clinical process. Third, the side effects of oncological treatment—such as fatigue, metabolic alterations, and immune function suppression—may impact training capacity and progression. To address this, the study incorporates a flexible approach to workload adjustment based on perceived exertion (RPE ≥7), allowing for load reductions when necessary to optimize safety and adherence (47, 48).

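### The discontinuation rule does not separate stopping the exercise programme from leaving the study, which permits selection bias of unknown direction in the week-8 SPPB comparison

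*Protocol article*

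**What the plan says.** Section 2.2 (Participants and eligibility criteria) opens its list with "Participants will be discontinued if they meet any of the following". The grounds include "Negative developments or progression of the tumor process", "Severe adverse events related to exercise", "Voluntary withdrawal from the intervention", new medical contraindications, and "Non-adherence to the intervention protocol that compromises study integrity". No adherence threshold is given, nobody is named to judge it, and the object of discontinuation (exercise or study) is not stated.

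Section 2.4 (Outcomes) provides one assessment after baseline: "After the intervention period, all outcome variables will then be evaluated again". The primary outcome, SPPB (section 2.4.1), is therefore measured once after randomisation, at the end of the 8 weeks.

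Section 2.5 (Sample size) arrives at 18 per group, "also assuming a loss rate of 15" per cent. Section 2.7 states that neither participants nor evaluators are blinded. Section 3.2 (Limitations) says that disease progression and tumour complications "may result in participant dropout".

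**The concern.** Two of the grounds make sense mainly as study exit. Someone who has already withdrawn from the intervention has nothing left to be discontinued from except the study. Stopping the exercise of someone who is not exercising achieves nothing either, and the reason given for the non-adherence ground is the integrity of the study, not safety. The Limitations section also connects one listed ground, progression, with dropout.

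The removals would be related to the outcome on the article's own account. The Introduction ties fatigue to muscle weakness and loss of physical function, and the Discussion names fatigue and exhaustion as main complications of the programme. People who stop or fall behind are therefore plausibly those with lower SPPB. The removals also happen after randomisation, in an open-label trial, under a criterion without a definition.

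What is at stake is whether the primary comparison remains a comparison of the groups as randomised. This is a rule of conduct, so a later analysis plan cannot repair it: a week-8 SPPB that was never measured cannot be recovered by naming an analysis population.

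**Working it through.** **Inputs from the article.** Target difference 1.34 SPPB points, SD 1.3, alpha 0.05, power 80%, 15% losses, 18 per group (section 2.5); 36 in total (Abstract).

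**Input assumed.** The correlation ρ between the propensity to be removed and a poor SPPB is taken as 0.3 to 0.7. The number removed in each arm is also assumed. Neither is in the article.

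**Step 1: the stated sample size.** n = 2 × [SD × (z₀.₉₇₅ + z₀.₈₀) / Δ]² = 2 × [1.3 × (1.960 + 0.842) / 1.34]² = 14.77, rounded up to 15. With 15% losses, 15 / 0.85 = 17.6, rounded up to 18. The stated figure reproduces with a two-sided alpha. It leaves room for 18 − 15 = 3 losses per arm, which is the number used below.

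**Step 2: approximate bias if the removed are not measured.** If the fraction f with the highest propensity for removal leaves one arm, the mean of those remaining shifts by SD × ρ × φ(c) / (1 − f), where c = Φ⁻¹(f). With f = 3/18, c = −0.967 and φ(c) = 0.250, so the shift is 1.3 × ρ × 0.250 / 0.833 = 0.39ρ:
- ρ = 0.3: 0.12 points
- ρ = 0.5: 0.19 points
- ρ = 0.7: 0.27 points

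**Step 3: simulation at the actual sample size.** 40,000 trials for each setting, 18 per arm, no true effect, SD 1.3, t-test on those remaining. Each cell gives the mean bias in SPPB points (positive favours the supervised arm), then the two-sided rejection rate at 0.05.

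| Removed: supervised / control | ρ = 0.3 | ρ = 0.5 | ρ = 0.7 |
|---|---|---|---|
| 3 / 0 | +0.11; 5.8% | +0.19; 7.2% | +0.26; 9.3% |
| 0 / 3 | −0.11; 5.8% | −0.18; 6.9% | −0.26; 9.5% |
| 3 / 3 | 0.00; 5.3% | 0.00; 5.6% | 0.00; 6.5% |
| 5 / 1 | +0.13; 6.0% | +0.22; 8.1% | +0.31; 11.4% |
| 1 / 5 | −0.13; 5.9% | −0.22; 8.1% | −0.31; 11.3% |

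Against the 1.34-point target, 0.11 is 8% and 0.26 is 19%. The sign follows whichever arm loses more.

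**Step 4: what complete follow-up does to power.** With all 18 per arm assessed, t-test power for 1.34 at SD 1.3 is 0.85; with 15 per arm it is 0.78. This assumes that non-adherence does not dilute the effect.

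**The case against.** The article says only that participants are discontinued. It does not say that they go unmeasured or are left out of the analysis. Section 2.4 promises reassessment of all outcomes with no exception for people who stop training, and the assessment schedule in Supplementary Table S1 is not at hand. Section 2.8 names no completer or per-protocol analysis, and an analysis population may properly be left to a fuller document. The non-adherence ground is also qualified: it applies only where study integrity suffers, not to every missed session. All of this stands, and it makes the bias conditional on the natural reading of section 2.2. It does not remove the ambiguity in the rule itself.

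A reader might go further and infer that the bias favours the supervised arm, because its 16 sessions (2 × 8 weeks) are demanding and observed by a physiotherapist. The article does not support that. Section 2.3.2 gives the control arm its own programme, home exercise on 5 days a week plus an hour's walk every day, without supervision, and no ground in section 2.2 is tied to one arm. Control participants could be discontinued as often or more often.

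A reader might also infer that the 15% loss rate is there to absorb these removals. Section 2.5 gives no cause for it.

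**Conclusion.** The concern holds as a defect in a stated rule. Section 2.2 runs together stopping the exercise and leaving the study, and it adds an undefined non-adherence ground. Followed in its natural sense, it would remove people for outcome-related reasons after randomisation and before the only follow-up SPPB. The result is a risk of selection bias of unknown direction.

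The size is small to moderate. With 3 of 18 lost in one arm only, it is about 0.11 to 0.26 points, or 8% to 19% of the target difference, with type I error of about 6% to just over 9%. With equally selective loss in both arms the mean bias is about zero. These figures rest on the assumed ρ, on the assumed arm-specific losses, on every loss being selective, and on discontinued participants not being measured. Losses unrelated to outcome would reduce the bias.

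The documents do not show that randomisation is already compromised, that the analysis excludes anyone, or that the supervised arm would benefit.

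**What to change.** - Reword section 2.2 so that the listed criteria end participation in the exercise programme only. The safety stopping rules stay as they are.
- Delete non-adherence as a ground for removal from the study. Record adherence in both arms instead.
- State that every randomised participant is invited to the already planned week-8 assessment unless consent to data collection is withdrawn.
- Make the comparison by assigned arm primary, with any analysis restricted to adherers as sensitivity only.

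The cost is a wording amendment and some week-8 visits for people who have stopped training. The estimate may be somewhat diluted by non-adherence, because it then describes the effect of being assigned to the programme. The sample size of 36 need not change.

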### Intervention

2.3

The exercise intervention program has been tailored for participants diagnosed with CLL undergoing active treatment. To ensure appropriate methodological quality and replicability of the exercise program, the Consensus on Exercise Reporting Template (CERT) (25) guidelines will be followed for a detailed description of the intervention (Supplementary Table S2). It primarily emphasizes resistance training, while also incorporating daily aerobic activities. This intervention will span a duration of 8 weeks. The study sample will be randomly split into two groups: the intervention group and the control group, as described below.

#### Intervention group

2.3.1

The intervention group will engage in a supervised resistance training program twice a week, along with a home-based physical activity promotion program to be completed three times a week. All supervised training sessions will be led by a physiotherapist at a healthcare facility.

##### Supervised training sessions

2.3.1.1

There will be two weekly sessions, each one lasting 50 min. Each session will have three distinct parts:
-Warm-up: Begin with 10 min of full-body strength and aerobic exercises focusing on the muscle groups that will be targeted in the upcoming session. Exercise intensity will be monitored using the 0–10 Rating of Perceived Exertion (RPE) scale, following the recommendations of the American College of Sports Medicine (26), participants will be required to maintain a perceived effort of at least 6 on the RPE scale.-Resistance Training: Participants will perform six resistance exercises targeting the major muscle groups over a 30-minute period. The initial load will be set at 70% of the estimated one-repetition maximum (1-RM). When a participant successfully completes three sets of 12 repetitions at this weight for two consecutive sessions, the load will be increased by 10%. The exercises will follow a circuit format, with 30 s of rest between exercises and 90 s of rest between sets. Exercise intensity will be monitored using the 0–10 RPE scale, following the recommendations of the American College of Sports Medicine. To ensure an adequate training stimulus, participants will be required to maintain a perceived effort of at least 7 on the RPE scale. This approach allows for a precise regulation of exercise intensity, considering individual variations in training response and ensuring sufficient overload for adaptation. For exercises that include jumps, such as Sit-to-Stand Jumps, Single-Leg Box Step-Ups, and Jump Squats, only body weight will be used initially. These exercises will not progress based on 1RM but will be adjusted following RPE, ensuring that participants maintain an appropriate intensity while minimizing the risk of injury-Cooldown/Mobility: Finish with 10 min of a combination of deep breathing exercises and global mobility work to promote recovery.The following describes the four training sessions, which will be repeated in order and cyclically until the 8 weeks of training are completed.

###### Session 1

2.3.1.1.1

1.Warm-up (10 min)
•2 min: Walk in circles taking advantage of the width of the room incorporating mobility exercises.
○20 s: Just walk fast.○20 s: Walk with a long stride.○20 s: Shoulder circles backward.○20 s: Alternating knee lifts to chest.○20 s: Walk on tiptoes.○20 s: Lateral movement with jogging.•2 min: Single-leg balance with slight knee and hip flexion, 1 min on each leg.•1 min: Wall/floor push-ups.•1 min: Wall sit.•2 min: Skipping.•2 min: Partner ball throws or wall throws.2.Resistance Training
•Bodyweight squat.•Romanian deadlift.•Abdominal plank (3 set of 30 s).•Bench press with barbell.•Bicep curls dumbbells + shoulder flexion.•Dumbbell rows.

**There will be 6 stations, and participants will rotate from one to the next until completing all 6 exercises. They will do 3 sets of 12 repetitions at 70% of 1RM. For unilateral exercises, 3 sets of 12 repetitions will be performed on each side. Rest 30 s between stations and at the end of each complete set, rest for 90 s*.
3.Cool-down
•3 min: Slow-paced walking with diaphragmatic breathing.•1 min: Quadriceps stretch.•1 min: Hamstring stretch.•1 min: Calf stretch.•1 min: Bicep stretch.•1 min: Shoulder stretch.•2 min: Seated cervical mobility exercises.

###### Session 2

2.3.1.1.2

1.Warm-up (10 min)
•2 min: Walk in circles taking advantage of the room's width incorporating mobility exercises.
○20 s: Just walk.○20 s: Shoulder abduction/adduction in transverse plane.○20 s: Alternating shoulder flexion/extension.○20 s: Leg lifts with straight knees alternately.○20 s: Walk on tiptoes.○20 s: Jumping in place.•2 min: Ankle proprioception on single-leg support, 1 min on each leg.•1 min: Knee lift with contralateral arm raise.•1 min: Bodyweight squats/sit and stand from a chair.•2 min: Step-up with contralateral knee raise.•2 min: Boxing (punching forward with alternate arms at a slow pace).2.Resistance Training
•Forward lunge with sandbag/dumbbell/kettlebell.•Hip thrust with barbell/kettlebell.•Pallof press with resistance band.•Dumbbell bench press.•Dumbbell shoulder press.•Sit-to-stand jumps.

**There will be 6 stations, and participants will rotate from one to the next until completing all 6 exercises. They will do 3 sets of 12 repetitions at 70% of 1RM. Rest 30 s between stations and at the end of each complete set, rest for 90 s*.
3.Cool-down
•3 min: Slow-paced walking with diaphragmatic breathing.•1 min: Quadriceps stretch.•1 min: Glute stretch.•1 min: Adductor stretch.•1 min: Hamstring stretch.•1 min: Shoulder stretch.•2 min: Seated cervical mobility exercises.

###### Session 3

2.3.1.1.3

1.Warm-up (10 min)
•2 min: Walk in circles taking advantage of the room's width incorporating mobility exercises.
○20 s: Just walk.○20 s: Elbow flexion/extension.○20 s: Shoulder abduction/adduction.○20 s: Hip flexion + abduction.○20 s: Walking lunges.○20 s: Side steps.•2 min: Lateral step-ups, 1 min on each leg.•1 min: Close-grip push-ups on wall/floor.•1 min: Bodyweight alternating lunges in place.•2 min: Jumping jacks.•2 min: Bodyweight glute bridges.2.Resistance Training
•Wide stance squat.•Deadlift.•Barbell rows.•Barbell bicep curls.•Dumbbell lateral shoulder raises.•Single-leg box step-ups.

**There will be 6 stations, and participants will rotate from one to the next until completing all 6 exercises. They will do 3 sets of 12 repetitions at 70% of 1RM. Rest 30 s between stations and at the end of each complete set, rest for 90 s*.
3.Cool-down
•3 min: Slow-paced walking with diaphragmatic breathing.•1 min: Quadriceps stretch.•1 min: Glute stretch.•1 min: Hamstring stretch.•1 min: Bicep stretch.•1 min: Shoulder stretch.•2 min: Seated cervical mobility exercises.

###### Session 4

2.3.1.1.4

1.Warm-up (10 min)
•2 min: Walk in circles taking advantage of the room's width incorporating mobility exercises.
○20 s: Just walk.○20 s: Squat and stand up as you walk.○20 s: Trunk rotations with shoulder push.○20 s: Shoulder raises.○20 s: Side lunges.○20 s: Walk backward.•2 min: Sit and stand from a chair.•1 min: Theraband elbow flexion.•1 min: Calf raises and holds statically.•2 min: Jumping in place.•2 min: Shoulder circumduction with light weight.2.Resistance Training
•Lateral lunge with kettlebell.•Deadlift.•Incline bench chest fly with dumbbells.•Supine triceps press.•Front shoulder raises with plate.•Jump squats.

**There will be 6 stations, and participants will rotate from one to the next until completing all 6 exercises. They will do 3 sets of 12 repetitions at 70% of 1RM. Rest 30 s between stations and at the end of each complete set, rest for 90 s*.
3.Cool-down
•3 min: Slow-paced walking with diaphragmatic breathing.•1 min: Quadriceps stretch.•1 min: Glute stretch.•1 min: Triceps stretch.•1 min: Chest stretch.•1 min: Shoulder stretch.•2 min: Seated cervical mobility exercises.

